## Discussion

This paper outlines the protocol for a multicentre RCT that will compare the effect of a combination of manual therapy and exercise therapy, exercise therapy only and a waiting-list control on physical function in osteoarthritis of the hip. A multicentre approach was chosen to maximize the sample size and to improve generalisability of the results. This study is in keeping with Meinert's definition of multi-centre, where the data are acquired from two or more settings that are organizationally independent, a common intervention and data-collection protocol are used, and data management and analysis are centralized [94]. Although the setting of the four centres is similar, there may be differences in the demographic and socioeconomic profile between the sites, which are located in different geographical areas within an urban setting.

A number of methodological elements have been included in the trial to minimize bias such as power calculation, randomization, concealed allocation, blinded outcome assessment and intention-to-treat analysis. The reporting of the study will be in keeping with CONSORT guidelines [51], including recent recommendations for the reporting of non-pharmacological studies [52].

A distinctive feature of the study is the inclusion of a waiting-list control group. This is a variation of a cross-over trial, where the participants in the control group are crossed over to one of the intervention groups after the 9 week follow-up assessment. This design was chosen, as one of the inclusion criteria for participation in the trial was that all subjects must have been referred for physiotherapy, and consequently must receive treatment. As the waiting times for physiotherapy at the four participating sites can vary between 6–12 weeks, this waiting-list control group will not be unduly compromised in their waiting times for treatment. A true control group can result in higher dropouts as patient expectations are not met and implementing a cross-over design may help to reduce dropout rates in studies investigating chronic diseases such as arthritis [95]. The decision to include a control group was made because, although exercise therapy has been shown to have a positive short term effect on pain and function in hip OA, the specific exercise protocol in this study has not previously been investigated. Both exercise and manual therapy protocols are based on current clinical practice identified through questionnaire survey [19] and therefore should be easily implemented in a clinical setting. The waiting-list control group will improve the scientific rigour of the study and allows more definite conclusions to be made regarding the effect of the two interventions under investigation. The control group patients will be re-randomised into one of the two intervention groups after the 9 week follow-up. A similar design was used by Fransen et al [91,96]. Statistical analyses will be conducted on the two intervention groups, with and without the re-randomised control group subjects, to assess the effect of the 9 week waiting period on outcomes.

A combination of self-report and physical outcome measures will be used, all of which are easy to administer in a standardized manner across the four sites.

A secondary aim of this trial is to ascertain the effect of a number of baseline variables on treatment outcome of the two interventions under investigation. Effect of treatment may be different for patients with specific characteristics. Identification of factors that affect treatment response is increasingly being recognized as an important aspect of physiotherapy management as it may facilitate the development of more tailored rehabilitation regimes [97-99]. This is particularly relevant in OA which is described as a heterogenous condition [100]. The EULAR evidence-based recommendations for the management of hip OA identified that clinical predictors of response to pharmacological and non-pharmacological interventions for hip OA was one of 10 future research topics which should be undertaken [22].

In summary, this multi centre RCT will be undertaken to compare the effect of a combination of manual therapy and exercise therapy, exercise therapy only, and a waiting-list control on physical function in hip OA. High quality methodology will be used in keeping with CONSORT guidelines. The results of the study should inform clinical practice and add to the evidence base for physiotherapy-based interventions in hip OA.

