### Randomisation

Two computer generated randomisation lists have been drawn up by a statistician who is independent of the study. The first list will be used to randomize participants into one of the three arms of the trial. The second list will be used to re-randomise those subjects in the control group into one of the two intervention groups after the 9 week follow-up assessment. Both lists will be maintained by a member of the research team (TC) who will not be involved in the assessment or treatment of the participants.

Once informed consent has been obtained and baseline outcome measures have been completed, each participant will be randomly allocated to one of 3 groups

a. Exercise therapy

b. Exercise therapy and Manual Therapy

c. Control group (Waiting List)

Simple randomisation will be conducted. Group allocation will be communicated to the treating therapists in each treatment centre by the independent randomiser.

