### Outcome Measures

Patients will be assessed at baseline, 9 weeks (end of treatment for the intervention groups) and 18 weeks (end of treatment for the control group) by the blinded assessor in the physiotherapy department of each hospital. Subjects in the control group will have an additional follow-up at 27 weeks (18 weeks post treatment) (Fig 1). Subjects and treating therapists cannot be blinded to treatment allocation due to the nature of the interventions.

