### Statistical Analyses

These will be blinded and will be performed in consultation with a statistician. Baseline and demographic data will be presented using descriptive statistics. Differences from baseline will be calculated for all primary and secondary outcomes. Mean differences, standard deviations and 95% confidence intervals will be calculated for all continuous outcomes. A longitudinal repeated measures design will be used to assess change from baseline and to make between group comparisons for the continuous outcome measures. Comparisons will be made between the 3 groups at the 9 week period. Participants in the control group will be analysed according to the intervention received after the 9 week follow-up and comparisons will be made between the 2 intervention groups at 18 weeks (both with and without the re-randomised control group subjects at the 18 week period). This will be done on an 'intention to treat' basis. Participants will be analysed in the intervention groups to which they were originally assigned and will include withdrawels and patients not treated by the assigned intervention. Missing data will be replaced using the last observation carried forward. Per-protocol analyses will also be performed by excluding patients with deviations from the treatment protocol.

At the 9 week and 18 week time points, continuous variables will be analysed using a mixed ANOVA model (with treatment as the between group factor and time as the repeated factor), or the non-parametric equivalent if non-normal distributions apply. Where significant differences occur, post-hoc comparisons will be conducted using Tukey's multiple comparison procedure. Differences in nominal/ordinal data will be analysed using the χ^2 ^test. A significance level of 0.05 will be set for any inferential statistics conducted.

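### Comparing the two interventions with and without the re-randomised controls cannot show the overall effect of the 9-week wait, because a waiting effect common to both interventions drops out of that contrast on average

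*Protocol article*

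**What the plan says.** The Discussion gives the paired analyses a purpose. The two intervention groups are to be analysed "with and without the re-randomised control group subjects, to assess the effect of the 9 week waiting period on outcomes".

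The Statistical Analyses section gives the method. Former controls are pooled by treatment: "Participants in the control group will be analysed according to the intervention received after the 9 week follow-up". The with/without wording is attached to the between-intervention comparison: "comparisons will be made between the 2 intervention groups at 18 weeks (both with and without the re-randomised control group subjects at the 18 week" visit). The model is a "mixed ANOVA model (with treatment as the between group factor and time as the repeated factor"). Neither section names having waited as a factor or contrast.

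The Randomisation section says how former controls reach their arm: "The second list will be used to re-randomise those subjects in the control group into one of the two intervention groups". It adds: "Simple randomisation will be conducted".

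Outcome Measures sets the visits: "9 weeks (end of treatment for the intervention groups) and 18 weeks (end of treatment for the control group"). It then adds: "Subjects in the control group will have an additional follow-up at 27 weeks (18 weeks post treatment) (Fig 1").

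**The concern.** The question and the method do not match. The question is whether waiting nine weeks changes outcomes. The method estimates exercise plus manual therapy minus exercise, twice, on overlapping sets of patients. Former controls are spread at random over both arms, so a harm or benefit of waiting that does not depend on the later intervention enters both arm means and is subtracted away.

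At stake is the reading of the result. The two estimates could agree closely while delay had a large effect, and a reader of the purpose clause could take the agreement as evidence that waiting is harmless. They could also disagree for reasons unrelated to waiting. The first randomisation does create a comparison that addresses the question directly.

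**Working it through.** **Inputs.** Sample Size Considerations: difference 5.4 points, SD 11, two-sided 0.05, power 80%, 67 per group, 74 after 10% attrition, 50 enrolled per group, 150 in total. Assumptions: former controls are re-randomised 1:1 (no ratio is stated), giving 50 immediate and 25 former controls per intervention, 75 in all; the waiting effects used below are illustrative.

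**The plan's own figure.** The normal approximation gives 2 × (11 × (1.96 + 0.842) / 5.4)² = 65.1, so 66. The t-based solution is 66.1, so 67, as stated. For attrition, 67 × 1.1 = 73.7 gives the stated 74; 67 / 0.9 = 74.4 would give 75. SD 11 is therefore a fair working value.

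**What the pair responds to.** Let w be a waiting effect common to both interventions and g the extra effect of waiting in the exercise-plus-manual arm. Let pM and pE be the shares of former controls in the exercise-plus-manual and exercise arms. Then

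contrast with former controls − contrast without = w × (pM − pE) + g × pM.

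With equal shares, pM = pE = 25/75 = 1/3:

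| Common effect w | Modification g | Shift in contrast |
|---|---|---|
| 2, 5.4 or 10 | 0 | 0 |
| 0, 2, 5.4 or 10 | 2 | 2/3 = 0.67 |
| 0, 2, 5.4 or 10 | 5.4 | 5.4/3 = 1.80 |

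Simulation agreed: mean shift 0.00 for w = 5.4 and w = 10 with g = 0, and 1.80 for g = 5.4.

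**Unequal shares.** Simple randomisation equalises pM and pE only on average. Over 200,000 simulated allocations, pM − pE had mean 0, SD 0.077 and a 95% range of about −0.15 to +0.15. A common effect of 5.4 points could then leak in by about 5.4 × 0.15 = 0.8 points in either direction. The direction is set by chance, so the leak does not estimate w.

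**Power for modification.**
- SE of the contrast without former controls: 11 × √(2/50) = 2.20.
- SE with them: 11 × √(2/75) = 1.80.
- SE of the difference between the two estimates: √(2.20² − 1.796²) = 1.27.
- For g = 5.4: 1.80 / 1.27 = 1.42, and Φ(1.42 − 1.96) ≈ 0.29.

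**Time since treatment.** At week 18 former controls are at the end of treatment, and the original arms are about 18 − 9 = 9 weeks past it. Suppose waiting has no effect at all, but the difference between the interventions fades by 5.4 points over those nine weeks. The former controls' contrast then exceeds the original arms' contrast by 5.4, and the pooled contrast moves by 5.4/3 = 1.80. That is the same shift as a 5.4-point modification by waiting, and the pair cannot tell them apart.

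**The direct comparison.** Immediate against delayed starters, classed by first randomisation:
- No loss (100 v 50): SE = 11 × √(1/100 + 1/50) = 1.91; power for 5.4 points is about 81%.
- 10% loss (90 v 45): SE = 11 × √(1/90 + 1/45) = 2.01; 95% half-width 1.96 × 2.01 = 3.9.
- 90 v 40: SE = 11 × √(1/90 + 1/40) = 2.09; half-width 4.1.

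**Matching visits.** Delayed starters begin treatment after week 9. Their week 18 is 18 − 9 = 9 weeks from start, matching the immediate arms' week 9. Their week 27 is 27 − 9 = 18 weeks from start, matching the immediate arms' week 18. Week 27 is only 27 − 18 = 9 weeks after the end of their treatment, so the label in Outcome Measures fits only if counted from the start of treatment.

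**The case against.** The strongest objection is that the Discussion speaks of statistical analyses of the two groups in general. The Statistical Analyses section also plans changes from baseline with means, SDs and confidence intervals. If these within-arm changes were reported both ways, they would move with a common waiting effect, by about one third of it (5.4/3 = 1.8 points). This stands in part. However, the with/without wording is attached to the between-intervention comparison, which is the more natural reading, and a within-arm shift at week 18 would still be mixed with time since treatment.

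Three stronger readings are tempting, and the document does not support them.
- *Any effect of waiting cancels, so sensitivity is nil.* A modification of the treatment difference survives at about one third, and cancellation of a common effect is exact only with equal shares.
- *The trial would declare that waiting has no effect whenever the two analyses agree.* No such rule is stated. It is a likely misreading, not a planned conclusion.
- *The delayed-start comparison is missing and the 27-week visit unused.* A journal article condenses a fuller document that may cover both. The fault lies in the stated purpose of a stated analysis.

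It is also fair to say that waiting is neither the primary nor the secondary aim. The 6–12 week queues are mentioned to justify the control group, and no treatment conclusion depends on this clause.

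**Conclusion.** The point holds in this limited form. The with/without pair, as the Statistical Analyses section fixes it, cannot estimate the overall effect of the 9-week wait. A common effect of 2, 5.4 or 10 points shifts the contrast by 0 in expectation. At most the pair shows whether waiting modifies the difference between the interventions, at one third of its size, with about 29% power for 5.4 points, and confounded with time since treatment. If the 18-week time point were meant as time from start of treatment, that confounding would go but the cancellation would remain.

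These sizes rest on SD 11, 1:1 re-randomisation and the planned 50 and 25 per intervention. The three-group comparison at week 9 is unaffected. The point is minor for the primary result but worth correcting, because the protocol states a question together with a method that cannot answer it.

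**What to change.** 1. In the Discussion, replace the stated purpose: describe the with/without pair as a sensitivity analysis of the between-intervention contrast, and say that agreement between the two is not evidence about the effect of waiting.

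2. If the effect of waiting is to be assessed, compare immediate with delayed starters by first randomisation at equal time from start of treatment: immediate week 9 with delayed week 18, and immediate week 18 with delayed week 27. Adjust for the week-0 score and the intervention, add an intervention-by-delay term, and label the analysis exploratory.

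3. Reconcile the description of the 27-week visit with the stated end of treatment at week 18, so that the matching of visits is clear.

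The cost is a wording change and one secondary analysis on data already to be collected, with no new patients or visits. The downside is imprecision: a 95% interval of about ±4 points against a clinically important difference of 5.4. That assumes about 10% loss, a rate the protocol gives only for week 9, so the later comparison may be less precise.
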